Unlike prior studies using VR as a reaction to treat health disturbances, the protocol described in this manuscript, *Nurturing Moms*, is designed as a *preventative* measure for Latina and African-American mothers. NurtureVR, a digital maternal mental health program, developed by BehaVR, was designed to: a) guide mothers through pregnancy via education and empathy and b) help them identify and address potential mental health concerns before these become major barriers to maternal and infant health and well-being. There is minimal research using therapeutic VR for maternal mental health in a diverse group of expecting mothers. Such work is timely, as the scientific community has only recently begun to address the importance of including diverse populations in research (25, 26). This is particularly applicable to digital health research, as the United States healthcare system continues to rapidly integrate technology into patient care. Considering this, researchers and clinicians must make a conscious effort to ensure digital health tools are accessible to all populations, especially those who have been historically neglected by the healthcare system (27).

*The Nurturing Moms* protocol (NurtureVR) addresses the aforementioned gaps in the literature by exploring Latina and Black perinatal mental health and related factors. Our primary objective is to assess whether NurtureVR reduces stress levels and mental health symptoms of pregnant and postpartum Black and Latina women. Our secondary objective is to assess whether NurtureVR improves sleep, as well as pregnancy and childbirth experiences. Our tertiary objective is to examine whether NurtureVR improves pregnancy/postpartum health literacy. We hypothesize that NurtureVR’s combination of mindfulness, relaxation, and education will be protective against postpartum depression, beneficial for pregnancy and birth experiences, and increase health literacy.

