## Methods

### Study design overview

*Nurturing Moms* is a pre-and post-design study aimed at reducing stress among expectant and postpartum Black and Latina women through a 5-week exposure to NurtureVR, a virtual reality based digital therapeutic. NurtureVR is a digital maternal mental health and educational program combining mindfulness techniques, relaxation, and virtual reality-guided imagery of pregnant and postpartum experiences. The study was designed to address pregnant women and postpartum mothers experiencing serious psychological symptoms, specifically in the Black and Latina population where mental distress rates are disproportionately higher compared to the general population. Advanced digital solutions can be leveraged to provide quality maternal mental health care that is effective and accessible to all.

The study is driven by three objectives: 1) to assess whether NurtureVR reduces stress levels and mental health symptoms of pregnant and postpartum Black and Latina women; 2) evaluate whether NurtureVR improves sleep, as well as pregnancy and childbirth experiences; and 3) investigate whether NurtureVR improve pregnancy/postpartum health literacy.

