### Data collection

#### Baseline and follow-up

After being screened and providing consent for the study, participants will receive an email with a link to complete the baseline survey online via REDCap. This survey includes questionnaires and well-validated scales that collect data on demographics, health history, stress levels, experiences of discrimination, sleep quality, emotional support, and overall pregnancy experience (see **Table 2**). Study team members may help the participant complete the baseline survey over the phone, on Zoom, or in person if necessary.

**Table 2 T2:** Study measures.

Variable*	Baseline	3 months	1 year
Tracking Form and Demographic Questionnaire	x		
Pregnancy Health History or Prenatal Screening Questionnaire (28)	x		
Perceived Stress Scale (29)	x	x	x
Everyday Discrimination Scale (Short Form) (30, 31)	x		
PROMIS^®^ Item Bank v1.0–Sleep Disturbance–Short Form 4a (32)	x	x	x
PROMIS^®^ Item Bank v2.0–Emotional Support–Short Form 4a (33)	x	x	x
Maternal Self-Efficacy Questionnaire (34)	x	x	x
Pregnancy Experience Scale (PES) (35)	x		
Childbirth Experience Questionnaire (CEQ) (36)	x		
Edinburgh Postnatal Depression Scale (EPDS) (37)	x		
User Experience Questionnaire (38)	x		
Virtual Reality Neuroscience Questionnaire (VRNQ) (39)	x		

*Some of these questionnaires have questions about the father. As the father is not relevant and is not a secondary participant in this study, these questions referring to the father have been removed.

Participants will be invited to complete the same survey three months following the completion of the intervention and will be monitored for 1 year. There will also be an optional 1-year follow-up (See **Figure 3**).

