### Study instruments

Tracking Form and Demographic Questionnaire: This form consists of two questionnaires to collect demographic information including age, race, and sex. The forms also capture socio-economic information such as employment, education, income, zip code, and other geographical data.Pregnancy Health History or Prenatal Screening Questionnaire: This 3-page questionnaire developed by the American Medical Association can provide useful material to researchers and physicians who want to gather information either prior to pregnancy or during a pregnancy. This form can help determine the risk of a baby having chromosomal conditions or neural tube defects based on the parents’ family history. The form captures past medical history of the father and mother, mother’s history of pregnancies, and exposures during pregnancy (28).Perceived Stress Scale: The perceived stress scale developed in 1983 is a 10-item questionnaire used to gauge stress levels in individuals aged 12 and older. It examines the degree to which situations are perceived as stressful in terms of how unpredictable, uncontrollable, and overloaded respondents find their lives. Score ranges from 0 to 40, with higher scores representing higher levels of stress. Average scores are calculated by adding up the scores and dividing by the number of items, providing a useful indicator for evaluating the overall level of agreement on the likert scale (where 0 = Never, 1 = Almost never, 2 = Sometimes, 3 = Fairly often, and 4 = Very Often) The perceived stress scale has been shown to have a coefficient alpha reliability of.84,.84, and.86 in three studied samples with a test-retest correlation of.85 (29).Everyday Discrimination Scale (Short Form): The everyday discrimination is a five-item instrument measuring experiences of daily discrimination followed by a question about what the person believes was the reason for that daily discrimination. Responses are coded on a 6-point Likert scale ranging from ‘never ‘= 1 to ‘almost everyday’ = 6. Responses are summed across items to produce a score ranging from 10 to 60 (40). The everyday discrimination scale, developed by David Williams in 1997, has shown high levels of internal consistency, convergent validity and divergent validity among African American men and women, and has been widely used in studies of discrimination and health (30, 31).PROMIS^®^ Item Bank v1.0–Sleep Disturbance–Short Form 4a: The PROMIS Sleep Disturbance and Sleep-Related Impairment item banks were developed using a rigorous and systematic methodology, including literature reviews, qualitative item review, focus groups, cognitive interviewing, and psychometric testing. The short form was developed from the full 27-item bank and has been shown to have convergent validity, construct validity, and reliability similar to the full bank. The short form is an 8-item form measuring the quality of sleep and sleep disturbance over the past 7 days. Four items use an intensity scale (not at all, a little bit, somewhat, quite a bit, very much), three items use a frequency scale (never, rarely, sometimes, often, always), and one item (S109) assessing overall sleep quality uses a scale of very poor, poor, fair, good, very good (32).PROMIS^®^ Item Bank v2.0–Emotional Support–Short Form 4a: The PROMIS Emotional Support Short Form was developed by domain experts from the full bank to capture the range of traits and allow researchers to study secondary outcomes without full additional measures. It consists of 4 statements assessing perceived feelings of being cared for and valued as a person. Responses are coded on a 5-point Likert scale ranging from 1 = never to 5 = always. The convergent validity has been supported by strong correlations between the PROMIS Emotional Support short form and measures of similar constructs. Discriminant validity has also been confirmed by negligible correlations between the emotional support measure and measures of dissimilar constructs (33).Maternal Self-Efficacy Questionnaire: The Maternal Self-Efficacy Questionnaire consists of 10 statements assessing mothers’ confidence in their ability to perform parenting-specific tasks such as understanding the baby’s needs and feelings, talking, reading to and playing with the baby, and taking the baby for regular clinic/doctor check-ups. Responses are coded on a 4-point Likert scale (1 = much worse, 2 = somewhat worse, 3 = as good, 4 = better than others). The questionnaire has been found reliable, face and content validity have been shown to be adequate as well as internal consistency and test–retest reliability for the assessment of maternal self-efficacy (34).Pregnancy Experience Scale (PES): The pregnancy experience scale consists of 10 statements measuring how much different aspects of pregnancy have made the mother feel either uplifted and happy or upset and negative. Each response is rated from 0 = not at all to 3 = a great deal. Internal reliability, test-retest reliability, and convergent validity were comparable to the original 41-item PES developed in 2004 (35).Childbirth Experience Questionnaire (CEQ): The childbirth experience questionnaire consists of 22 statements assessing four domains of the childbirth experience; Own capacity, Professional support, Participation, and Perceived safety. It evaluates women’s experience of labor and childbirth, including their perceptions and feelings. For 19 of the items the response format is a 4-point Likert Scale whereas the last three items use a visual analogue scale (VAS). The scoring range is 1 to 4 where higher ratings reflect more positive experiences. The CEQ has demonstrated internal consistency, discriminant validity, equal item-hypothesized scale correlation, and item equal variance (36).Edinburgh Postnatal Depression Scale (EPDS): The Edinburgh Postnatal Depression Scale developed in 1987 remains a prominent tool for measuring postpartum depression. It consists of 10 statements which identify signs and symptoms of depression in the postnatal period. Responses are scored 0, 1, 2, or 3 according to increased severity of the symptom. Items marked with an asterisk (*) are reverse scored (i.e., 3, 2, 1, and 0). The total score is determined by adding together the scores for each of the 10 items. The EPDS demonstrates acceptable sensitivity, specificity and positive predictive value. It has been used in many studies, and has been introduced as a valuable and powerful postnatal depression screening tool in different cultures (37).User Experience Questionnaire: The User Experience Questionnaire consists of 26-items measuring whether people find the using the NurtureVR product to be an overall positive or negative experience. A seven stage scale is used between two opposing descriptors of the user experience. Mothers rate more closely to the descriptor they identify with (38).Virtual Reality Neuroscience Questionnaire (VRNQ): The Virtual Reality Neuroscience Questionnaire consists of 20-item questionnaire measuring the quality of user experience, game mechanics, and in-game assistance, as well as the intensity of the VR induced symptoms and effects. Responses are coded on a 7-point Likert scale, ranging from 1 = extremely low to 7 = extremely high. The higher scores indicate a more positive outcome (39).

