## Conclusion

In conclusion, the *Nurturing Moms* protocol aims to investigate the potential efficacy of NurtureVR, a virtual reality based maternal health and wellness program, in reducing stress among expectant and postpartum Black and Latina women. The disproportionate rates of psychological symptoms among this population, heightened by factors like economic hardships and limited access to psychoeducation, highlight the critical need for customized digital interventions. The present study aims to evaluate the effects of the NurtureVR program not only on maternal stress but also on improving sleep quality and enhancing health literacy during and after pregnancy. Our efforts to maximize the advantages of innovative digital solutions like NurtureVR, which incorporates mindfulness techniques, relaxation, and virtual reality-enabled guided imagery, aligns with recent evidence supporting the effectiveness of psychoeducation and early intervention in improving adverse mental health outcomes among expectant and postpartum women.

The pre-and post-study design provides participants with a holistic approach spanning pregnancy, labor and delivery, and postpartum phases. Implementing comprehensive learning modules, stress-coping mechanisms, and family involvement helps uplift mothers and nurtures the mental well-being of both mother and baby. The Nurturing Moms study not only spotlights the significance of interventions targeting maternal stress among minority populations but also contributes to the growing field of perinatal mental health by leveraging advanced digital solutions to support expectant and postpartum mothers.

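### Improved health literacy is the third stated objective and part of the hypothesis, but no listed instrument measures it at any time point

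*Protocol article*

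**What the plan says.** Health literacy is named as something the study will evaluate in several places in the protocol article:

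- Abstract, Objectives: listed last among the effects to be evaluated.
- Introduction, objectives: "Our tertiary objective is to examine whether NurtureVR improves pregnancy/postpartum health literacy".
- Introduction, hypothesis: the programme is expected to be "beneficial for pregnancy and birth experiences, and increase health literacy".
- Methods, Study design overview: the third of three numbered objectives is to "investigate whether NurtureVR improve pregnancy/postpartum health literacy".
- Conclusion: the evaluated effects include "improving sleep quality and enhancing health literacy during and after pregnancy".

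The measures are set out under Data collection. The Baseline and follow-up section says that the baseline survey covers "demographics, health history, stress levels, experiences of discrimination, sleep quality, emotional support, and overall pregnancy experience". Table 2 then lists 12 forms and questionnaires against three time points (baseline, 3 months, 1 year), and Study instruments describes them one by one. Four further rating scales, completed around the VR sessions, are described under Weekly mood state surveys.

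**The concern.** The objective asks whether the programme improves literacy. In a single-group before-and-after study, that needs a literacy or knowledge score from the same women before and after use. If no such score is collected, the question cannot be answered at any sample size or by any method of analysis.

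This matters more here than a stray tertiary aim usually would. The VR modules section makes education one of the programme's two main module categories, and Table 1 assigns education topics in every programme week, both before and after birth. The Statistical analysis plan section says that the data will supply effect sizes for larger studies. For literacy there would be none, and any later statement about it would have no measurement behind it.

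**Working it through.** The plan gives no figure for this objective, so there is nothing to recompute. The check was to go through every source of data the article describes and ask whether it yields a literacy or knowledge measure.

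| Source (section) | What it captures | Literacy or knowledge? |
|---|---|---|
| Demographic form (Table 2, Study instruments) | Socio-economic items, including education level; baseline only | No |
| Pregnancy health history form | Medical, family and pregnancy history; baseline only | No |
| Perceived Stress Scale | Stress | No |
| Everyday Discrimination Scale | Discrimination | No |
| PROMIS Sleep Disturbance | Sleep | No |
| PROMIS Emotional Support | Perceived support | No |
| Maternal Self-Efficacy Questionnaire | Confidence in parenting tasks | No |
| Pregnancy Experience Scale | Uplifting and upsetting aspects of pregnancy | No |
| Childbirth Experience Questionnaire | Experience of labour and birth | No |
| Edinburgh Postnatal Depression Scale | Depressive symptoms | No |
| User Experience Questionnaire | Experience with the product | No |
| Virtual Reality Neuroscience Questionnaire | VR quality and VR-induced symptoms | No |
| Four session scales (Weekly mood state surveys) | Anxiety, mood, pain, stress | No |
| Usage logs (VR modules) | Start times, time stamps, completion | No |
| Focus groups (Timeline) | Resilience, VR experience, recommendations | No |

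Count: 0 of 12 Table 2 entries and 0 of 4 session scales, at 0 of 3 time points.

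Four sources come closest, and none fills the gap:

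- **Maternal self-efficacy.** It is scheduled at all three time points, so a before-and-after comparison is possible. However, the instrument "consists of 10 statements assessing mothers’ confidence in their ability to perform parenting-specific tasks", and the mother rates herself against others. That is self-rated confidence. A woman can gain confidence without gaining knowledge, and the reverse.
- **Education level.** This is a background characteristic collected once. It cannot change in response to a 5-week programme.
- **Usage logs.** They show that a module was opened and finished. They do not show that anything was learned from it.
- **Focus groups.** There are two sessions of five women each, so 2 × 5 = 10 places against a planned 50 participants. Literacy is not a listed theme, and a discussion gives no before-and-after score.

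**The case against.** The strongest reply is that a journal article condenses a longer protocol, so a literacy scale may exist that the article does not name. There is some support for this. Table 2 is not a complete list of everything collected, because it leaves out the four session scales. The sentence summarising the survey content is looser still: it omits self-efficacy, depression, childbirth experience, user experience and the VR questionnaire, all of which Table 2 contains. Absence from that sentence alone therefore proves nothing.

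The reply does not carry the point. The session scales missing from Table 2 are described elsewhere in the article, whereas a literacy measure is described nowhere. The article gives a schedule of instruments by time point and then describes every entry, down to a family-history form. An unlisted scale serving one of three numbered objectives is unlikely.

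Three narrower objections do stand:

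- The Statistical analysis plan section gives no analysis for literacy, but a separate analysis plan could supply one. That gap is not counted here. The point rests on the missing measurement, which no analysis plan can repair.
- Nothing in the article suggests that the self-efficacy score will be presented as literacy. The remark about it is a caution.
- The Discussion says that the main aim is feasibility and acceptability, and literacy ranks third. The gap does not touch the stress outcome, the sample size or participant safety.

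**Conclusion.** The concern holds. As documented, the study plans no measurement of health literacy in any of its 50 women at any of the three time points, so one of three numbered objectives and the matching part of the hypothesis cannot be answered. The conclusion assumes that Table 2, the instrument descriptions and the session scales together list all outcome measures. If the full protocol contains a literacy scale, the article needs correcting to show it. The matter should be put right, but it does not threaten the primary objective.

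**What to change.** Choose one of two routes.

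**Remove the objective.** Take health literacy out of the abstract's objectives, the Introduction (objective and hypothesis), the Study design overview and the Conclusion, or state there that it is not assessed. This costs wording only and is available whatever the enrolment status, which the article does not give.

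**Add a measure.** Add a short health-literacy or knowledge scale to the baseline and follow-up REDCap surveys, enter it in Table 2 and Study instruments, and name its analysis. Three conditions apply:

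- It can give a before-and-after comparison only for women who have not yet completed baseline. If enrolment is well advanced, removal is the cleaner route.
- It must suit both groups. Table 1 gives separate prenatal and postpartum curricula, so a single set of questions tied to the modules would test many women on content they were not assigned.
- The protocol should say which construct is meant. Questions tied to the programme's own topics measure recall of its content, which is narrower than health literacy.

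The cost is an ethics amendment and some added time on a baseline survey already stated to take 10–20 minutes.

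Under either route, the self-efficacy score should not stand in for literacy.

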## Methods

### Study design overview

*Nurturing Moms* is a pre-and post-design study aimed at reducing stress among expectant and postpartum Black and Latina women through a 5-week exposure to NurtureVR, a virtual reality based digital therapeutic. NurtureVR is a digital maternal mental health and educational program combining mindfulness techniques, relaxation, and virtual reality-guided imagery of pregnant and postpartum experiences. The study was designed to address pregnant women and postpartum mothers experiencing serious psychological symptoms, specifically in the Black and Latina population where mental distress rates are disproportionately higher compared to the general population. Advanced digital solutions can be leveraged to provide quality maternal mental health care that is effective and accessible to all.

The study is driven by three objectives: 1) to assess whether NurtureVR reduces stress levels and mental health symptoms of pregnant and postpartum Black and Latina women; 2) evaluate whether NurtureVR improves sleep, as well as pregnancy and childbirth experiences; and 3) investigate whether NurtureVR improve pregnancy/postpartum health literacy.

### Study procedures

#### Timeline

The Nurturing Moms study will assess the effectiveness of NurtureVR, a digital solution for maternal mental health, across four phases. In phase I, participants will be recruited from health clinics, community-based organizations, and online platforms. Interested individuals will receive a screening form link via REDCap to determine eligibility based on inclusion and exclusion criteria (described below). Eligible participants will be contacted by a study team member to review and electronically sign an informed consent form before completing a 10–20-minute baseline questionnaire on the same platform.

In Phase II, VR headsets will be shipped to participants one week after the baseline questionnaire is completed. Participants will use the NurtureVR for five weeks and will be asked to rate their level of stress, anxiety, mood, and pain level after each VR session using well-validated scales. In Phase III, participants will repeat the surveys three months after completion of the digital intervention. Additionally, two focus group sessions will be held with five participants each, focusing on Black and Latina expectant and postpartum women’s views on resilience, their NurtureVR experiences, perceptions, and recommendations for using VR for stress management. Each focus group will be conducted online to ensure accessibility, with one session scheduled before and one after the participants’ completion of the NurtureVR program. Discussions will follow a semi-structured format, encouraging open dialogue around key themes such as resilience and VR experience. For data analysis, we will employ thematic analysis, using NVivo software to organize and code responses. This approach allows for consistent identification of recurring themes, patterns, and variations in participants’ feedback, facilitating a thorough understanding of their experiences and recommendations. Coding will be iterative and conducted by multiple researchers to enhance reliability and capture diverse perspectives.

The final phase, which is optional, invites participants to repeat the surveys one year after completing NurtureVR. This comprehensive approach aims to provide a thorough evaluation of NurtureVR’s impact on maternal mental health in the short and longer term (See **Figure 1**).

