**Methods:**

The Nurturing Moms study uses a pre- and post-intervention design with a 5-week NurtureVR program. Fifty participants, 25 expectant and 25 postpartum Black and Latina women, will be recruited through clinics, community organizations, and online platforms. The study involves three phases: baseline assessments of stress, mood, self-efficacy, demographics, and health history; daily use of NurtureVR for 15 minutes during the third trimester and six weeks postpartum; and follow-up assessments at six weeks postpartum. The program includes 49 modules on labor and delivery, stress during pregnancy, nutrition, breastfeeding, hormonal changes, 3D VR representations of fetal development, pain management simulations, and mindfulness exercises for labor. Participants will report stress, anxiety, mood, and pain levels following each VR session. Additional qualitative insights will be gathered through focus groups, and an optional survey will be administered one-year post-intervention to evaluate long-term effects.

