#### Participants

Participants in the *Nurturing Moms* study will be recruited through various channels: clinical/health settings, community outreach recruitment events and community organizations, Research Match, and UMiamiHealthResearch.org. Participants will undergo a screening process in which they must meet the following inclusion criteria: 18 years old or older, speaks and understands English, Black or Latina. Additionally, they must be pregnant (less than 36 weeks) or postpartum (up to 12 months after birth). Participants will be disqualified from inclusion in the study based on the following exclusion criteria: a diagnosis of psychosis, inability to speak or understand English, or being neither pregnant (>36 weeks) nor postpartum (up to 12 months). Individuals with a history of seizures, vertigo, significant vision or hearing impairment, significant motion sickness, epilepsy, or sensitivity to flashing light/motion are also excluded from participation. Injuries to the eyes, face, neck, or arms that would make the use of the hardware uncomfortable are also grounds for exclusion. The implementation of these criteria enhances internal validity, optimizing the relevance and reliability of research findings. We aim to enroll 50 participants (25 expectant and 25 postpartum).

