
#### NurtureVR

The NutureVR mobile app will be installed on the participants’ mobile device. With 49 modules, the program will span five weeks prenatal, optional use during labor, and five weeks postpartum (available for anyone up to six months after childbirth). These modules are aimed to serve as a sanctuary for learning and stress relief, offering education and support for the entire family while fostering intimate connections and bonding to benefit the well-being of the mother and baby. Key features of NurtureVR include education on the effects of stress during pregnancy, 3D VR representations of fetal development, pain management simulations, mindfulness exercises for labor, and postpartum guidance covering topics such as hormonal changes, nutrition, emotional regulation, breastfeeding, and lactation training through VR-enabled practice sessions.

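### The main follow-up is dated six weeks postpartum in the abstract but three months after completion in the methods, and completion is itself defined inconsistently, so change in stress among expectant women can be confounded with childbirth

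*Protocol article*

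**What the plan says.** Two dates are given for the main follow-up. The Methods paragraph of the abstract has "follow-up assessments at six weeks postpartum". The Timeline section says "participants will repeat the surveys three months after completion of the digital intervention", and the section Baseline and follow-up repeats this: women are invited to "complete the same survey three months following the completion of the intervention". Table 2 follows the methods text. Its header reads "Variable* Baseline 3 months 1 year", with no column for six weeks postpartum and none for the end of the programme. The one-year survey is optional.

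The end of the programme, from which the three months are counted, is described in three ways:
- Study design overview and Timeline: five weeks of use.
- Abstract: daily use in the third trimester and through six weeks after birth.
- NurtureVR section: "the program will span five weeks prenatal, optional use during labor, and five weeks postpartum".

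Entry is wide. The Participants section states: "they must be pregnant (less than 36 weeks) or postpartum (up to 12 months after birth". No lower gestational limit is given. The target is 25 expectant and 25 postpartum women in a single group. The statistical section plans a General Linear Model of stress over time in pregnant and postpartum women, and names age, parity, socioeconomic status and baseline mental health as covariates for regression adjustment.

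**The concern.** One anchor counts from birth and the other from the end of use, so they are not two wordings of the same date. The birth anchor cannot serve as a follow-up for much of the postpartum cohort. The end-of-use anchor moves with the definition of completion.

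In an uncontrolled pre-post study the change between two dates is the whole effect estimate. If some women give birth between the surveys and others do not, part of that change may reflect childbirth and the months after it rather than the programme. The statistical section says the data will supply effect sizes and sample sizes for larger studies, so an estimate with an unclear time point would carry forward into their design.

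**Working it through.** The plan states no interval from baseline to the main follow-up, so there is no figure of its own to reproduce. The check is calendar arithmetic.

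**Inputs from the article.** Shipping lag: "VR headsets will be shipped to participants one week after the baseline questionnaire is completed" (1 week). Use: 5 weeks (Timeline). Follow-up: three months after completion. Entry: under 36 weeks pregnant, or up to 12 months postpartum.

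**Assumptions.** Three months = 13 weeks; use starts on shipping; birth at 40 weeks, varied from 37 to 41.

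**1. The abstract's date in the postpartum cohort.** A woman enrolled w weeks after birth has her baseline at week w. Six weeks postpartum is after baseline only if w < 6. For w from 6 to 52 it is at or before baseline.

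**2. Five-week reading, expectant women.** With baseline at g weeks' gestation, the programme ends at g + 1 + 5 = g + 6 and the survey falls at g + 6 + 13 = g + 19.

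| Baseline (weeks) | Programme end | Three-month survey | State at survey, birth at 40 weeks |
|---|---|---|---|
| 12 | 18 | 31 | pregnant |
| 21 | 27 | 40 | due date |
| 28 | 34 | 47 | 7 weeks postpartum |
| 35+6 (35.86) | 41.86 | 54.86 | 14.9 weeks postpartum |

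The crossover is at g = 40 − 19 = 21 weeks. For birth at 37 to 41 weeks it lies at 37 − 19 = 18 to 41 − 19 = 22 weeks.

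**3. Do the two anchors ever agree?** Six weeks postpartum is week 46 on the same scale, which is 46 − (g + 6) = 40 − g weeks after programme end. That is 12 weeks for entry at 28 and 5 weeks for entry at 35. It equals 13 weeks only at g = 27.

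**4. Completion as the end of postpartum use, expectant women.** Counting postpartum use from birth:
- NurtureVR section: 5 + 13 = 18 weeks postpartum.
- Abstract: 6 + 13 = 19 weeks postpartum.

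Under either, every expectant entrant has delivered by the survey.

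**5. Five-week reading, postpartum women.** The survey falls at w + 19, that is from 19 weeks (w = 0) to 71 weeks (w = 52) after birth. These women are postpartum at both surveys.

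**6. The analysis.** None of the four named covariates is gestational age, time since birth, or delivery between surveys.

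**7. What is measured around programme end.** Table 2 schedules the Perceived Stress Scale at baseline, 3 months and 1 year. During use, the sections Timeline, VR modules and Weekly mood state surveys provide brief ratings of anxiety, mood, pain and stress around sessions.

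**The case against.** A reader might infer that the study never measures the effect at the end of the programme, or that stress is first looked at 13 weeks after use stops. The article does not support this. Stress is rated around VR sessions throughout use. What is absent at programme end is the Perceived Stress Scale and the other full questionnaires.

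A reader might also infer that the whole pre-post contrast mixes pregnant and postpartum states. The change of state can affect only the expectant half. The subgroup still pregnant at follow-up arises only under the five-week reading with early entry. The entry rule permits this, but the abstract's third-trimester use and the labour content of Table 1 point to later use. If use started at 28 weeks (taken here as the start of the third trimester), 28 + 5 + 13 = 46 weeks, and all would have delivered. This limits the claim that women differ in state at follow-up. It does not remove the concern, because those women still pass through childbirth between surveys while the postpartum cohort does not.

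It is tempting to make programme end the primary time point. The Introduction hypothesises protection against postpartum depression, which needs an assessment after birth, and many expectant women would still be pregnant at programme end. Nor would it fully separate the states: entry at 34 to 35 weeks puts programme end at 40 to 41 weeks.

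The Discussion concedes that without a control group attribution is difficult, and gives feasibility as the primary aim. Model terms may be set out in an analysis plan that is not shown, the covariate list is illustrative, and nothing says the cohorts are pooled without a group term. These points soften the modelling part. They do not touch the conflict of dates, and the Discussion does not mention childbirth between surveys. Figures 1 and 3 are not shown, but no figure could make both dates true.

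**Conclusion.** The point holds as a contradiction in the timing of the main outcome, and it needs correcting. The abstract's date is impossible as a follow-up for women enrolled from 6 to 52 weeks after birth. The methods' date is coherent in itself but rests on an end of programme that the article defines in three ways.

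For expectant women the three-month survey can fall anywhere from during pregnancy to about 15 weeks postpartum on the five-week reading, or at about 18 to 19 weeks postpartum if completion is the end of postpartum use. These figures rest on the assumptions listed in the working. Varying birth from 37 to 41 weeks moves the crossover only between 18 and 22 weeks at entry.

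The resulting confounding with childbirth is possible in 25 of the 50 women. Its size and direction cannot be derived from the article, which gives neither the expected distribution of gestational age at entry nor the expected course of stress across birth. The lack of a full questionnaire at programme end is a lesser design matter and not an error.

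**What to change.** 1. Reconcile the abstract, Timeline, Baseline and follow-up, Table 2 and NurtureVR sections to one follow-up anchor and one definition of completion that can be applied in both cohorts. Which schedule of use is intended is for the investigators to state. Cost: wording and an ethics-board amendment.
2. Record gestational age or days since birth at every survey. Cost: one or two items on the existing REDCap form.
3. Report change in stress separately for the expectant and postpartum cohorts, and adjust for delivery between surveys. Cost: some precision with 25 women per cohort. If nearly all expectant women deliver between surveys, the delivery term will be close to a cohort indicator, and the report by cohort then carries the information.
4. Optional: add a short REDCap survey with the Perceived Stress Scale and PROMIS sleep form at programme end as a secondary time point, keeping a later assessment for the postpartum hypothesis. Cost: one extra brief survey per participant.
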